## Abstract

Advances in imaging have changed prostate radiotherapy through improved biochemical control from focal boost and improved detection of recurrence. These advances are reviewed in the context of prostate stereotactic body radiation therapy (SBRT) and the ARGOS/CLIMBER trial protocol. ARGOS/CLIMBER will evaluate 1) the safety and feasibility of SBRT with focal boost guided by multiparametric MRI (mpMRI) and ^18^F-PSMA-1007 PET and 2) imaging and laboratory biomarkers for response to SBRT. To date, response to prostate SBRT is most commonly evaluated using the Phoenix Criteria for biochemical failure. The drawbacks of this approach include lack of lesion identification, a high false-positive rate, and delay in identifying treatment failure. Patients in ARGOS/CLIMBER will receive dynamic ^18^F-PSMA-1007 PET and mpMRI prior to SBRT for treatment planning and at 6 and 24 months after SBRT to assess response. Imaging findings will be correlated with prostate-specific antigen (PSA) and biopsy results, with the goal of early, non-invasive, and accurate identification of treatment failure.

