We plan to evaluate the safety of SBRT with PSMA PET/MRI-guided focal boost in a prospective early phase trial, “PSMA MRI Guided prOstate SBRT(ARGOS).” As noted, while the advanced imaging techniques described show promise for the characterization of primary or recurrent prostate cancer, no study has prospectively and longitudinally evaluated them after primary radiotherapy to characterize expected changes in response to treatment and to non-invasively identify early treatment failure. All patients in ARGOS will enter the translational component of the study Comprehensive, Longitudinal Evaluation of Imaging Biomarkers Post Radiotherapy (CLIMBER). We will use advanced imaging analysis techniques to evaluate longitudinal changes in a comprehensive battery of anatomic and functional prostate imaging panels using ^18^F-PSMA 1007 and mpMRI acquired prior to and after SBRT. ^18^F-PSMA-1007 is chosen given its favorable pharmacokinetics profile with primarily gastrointestinal elimination, reducing tracer accumulation in the bladder and allowing better visualization of prostate and pelvic lymph nodes. The knowledge obtained from ARGOS/CLIMBER will improve the understanding of imaging changes post-prostate SBRT and will have increasing clinical importance with increasing use of these techniques. The ARGOS/CLIMBER protocol as outlined below is due to open in early 2022, with a plan for accrual of 50 men over 3 years and with follow-up of up to 5 years for clinical endpoints.

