**Figure 2 f2:**
[figure not shown]
Example of focal dose escalation.

**Table 3 T3:** Dose constraints.

Structures and dose constraints (acceptable deviations)			
**Rectum**	V20Gy ≤ 50% (optimal) V28Gy ≤ 15% (20%) V32Gy ≤ 10% (15%) V35Gy ≤ 2 cc (4 cc) V38Gy ≤ 1 cc Dmax ≤ 40.6 Gy	**Bladder**	V20Gy ≤ 50% (optimal) V28Gy ≤ 15% (20%) V32Gy ≤ 10% (15%) V38Gy ≤ 6 cc V39.5Gy ≤ 2 cc
**Rectum_PRV**	Dmax ≤ 45 Gy	**Bladder_PRV**	Dmax ≤ 46 Gy (optimal)
**Urethra_PRV**	Dmax ≤ 52 Gy D10% ≤ 47.2 Gy D50% ≤ 42 Gy (optimal)	**Penile Bulb**	V20Gy ≤ 40% (90%) V35Gy ≤ 4%
**Bowel_Small**	V25Gy ≤ 20 cc (40cc) V30Gy ≤ 2 cc Dmax ≤ 3 5Gy	**Bowel_Large**	V25Gy ≤ 20 cc (40 cc) Dmax ≤ 38 Gy
**Femur_R and Femur_L**	V28Gy ≤ 5%		

The primary endpoints of the trial will be 6-week and 6-month gastrointestinal (GI) and GU toxicity using the Common Terminology Criteria for Adverse Events version 5.0 (CTCAE v5.0). While other prospective trials have confirmed the safety of an mpMRI-defined intra-prostatic boost with external beam radiotherapy (4, 6), the proposed boost volume in ARGOS/CLIMBER will be based on mpMRI and PSMA PET-targeted PET (17), and thus there is a need to demonstrate the safety of such a multi-modality defined boost volume. Secondary endpoints include Quality of life measured by the Expanded Prostate Cancer Index Composite (EPIC-26) questionnaires and 5-year disease-free survival (DFS) as a composite of BF, patient death, or development of clinical metastases or institution of salvage ADT.

All grade 3 or higher toxicity will be reported to the principal investigator. An independent data and safety monitoring board (IDSMB) will perform a formal interim analysis for safety and toxicity when half of the patients have been accrued or after 1 year, whichever comes first. The study will be discontinued if the projected rate of grade 3 or higher urinary or bowel toxicity exceeds 30%. IDSMB will meet at least annually to review trial data.

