Unique to the ARGOS/CLIMBER protocol is the integration of longitudinal imaging with PSMA-directed PET and mpMRI pretreatment and posttreatment. Serial PSMA PET/MR images will be collected at baseline, 6 months, and 2 years to characterize the imaging response of prostate cancer to treatment and potentially identify imaging biomarkers (including pharmacokinetics, radiomics, and quantitative PET and mpMRI metrics) that predict for 5-year DFS (**Table 4**). Additionally, baseline collection of diagnostic tissue biopsy samples and serial collection of blood and urine over multiple time points (baseline, 6 months, 1 year, and 2 years post-SBRT) will be performed for correlative biologic biomarker analyses with imaging changes, DFS, and toxicity posttreatment. Analysis of prostate biopsy at baseline and 2 years will allow for correlation of histopathology with PSMA PET/MR images. We will investigate whether a negative posttreatment PSMA PET/MRI is correlated with a negative 2-year posttreatment biopsy and long-term disease control (36, 39). We also plan to examine novel clinical prognostic biomarkers (i.e., absolute percentage of Gleason Pattern 4 on biopsy and 4-year PSA response rate) and their correlation with imaging findings and 5-year DFS.

**Table 4 T4:** Schedule of events.

Event	Weeks (week 0 is start of RT)										Q6mo (30–60mo)
	−3	−2	0	1 EOT	3	8 (6 weeks post-RT)	6 months post-RT	12 months post-RT	18 months post-RT	24 months post-RT	
	V1	V2	V3	V4	V5	V6	V7	V8	V9	V10	V11–15
Start alpha antagonists, simethicone	x										
Fiducial marker insertion		x									
Simulation and planning		x									
Treatment (5 fractions q2d, 10–12 days)			x	x							
CTCAE v5.0	x		x	x	x	x	x	x	x	x	x
EPIC-26 questionnaires	x		x	x		x	x	x	x	x	x
PSA and testosterone	x					x	x	x	x	x	
PSMA PET/MRI		x					x			x	
Liquid biomarker collection		x				x	x	x		x	
Transperineal biopsy		x								x	

CTCAE v5.0, Common Terminology Criteria for Adverse Events version 5.0; PSA, prostate-specific antigen; PSMA, prostate-specific membrane antigen.

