#### Disease-Free Survival

Five-year DFS will be determined as a composite of biochemical control, patient death or development of clinical metastases, or institution of salvage ADT. DFS will be estimated with a Kaplan–Meier (KM) curve, with the 5-year estimate extracted from the KM curve.

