#### Translational Imaging Endpoints

Changes in SUV metrics (SUVmax, SUVmean) within PSMA PET regions of interest (ROI) will be compared between the pre-RT PSMA PET and the 6-month post-RT PSMA PET. ROIs to be examined will include the dominant intra-prostatic lesions (DILs), the prostate as a whole, and, in the cases of men with PET-detected nodal disease, involved node ROIs. Descriptive statistics and diagrams (i.e., waterfall plots) will be used to characterize changes in SUV metrics. A linear mixed model with random intercept by an individual to account for the correlation present within individuals will be used to compare pretreatment vs. posttreatment SUV values at multiple timepoints. Overall response rates will be calculated in accordance with recent consensus guidelines (46).

Intra-prostatic mpMRI (T2W, DWI, and DCE-MRI) acquired pre-RT and 6 and 24 months post-RT will be reported by expert readers based on PI-RADS 2.1 and the complementary Prostate Imaging for Recurrence Reporting (PI-RR) system to identify intra-prostatic ROIs (44). Quantitative MRI metrics will be extracted, including ADC and pharmacokinetics parameters derived from dynamic PET and DCE-MRI. Radiomics approaches will be used to characterize the evolution of higher-level feature changes in PET and mpMRI over the course of treatment.

We will correlate changes in PET and mpMRI metrics at 6 and 24 months with 5-year DFS using linear regression models. We will also perform supervised machine learning to train support vector machines and random forest classifiers to predict response based on the pretreatment images. We will also perform a delta-radiomics analysis to predict response based on the radiomics trajectory computed from the first two time points. We will measure the performance of the classifiers using a cross-validation design, with metrics including the area under the receiver operating characteristic (ROC) curve and the error rate, false-positive rate, and false-negative rate computed at a point on the ROC curve that best balance the false-positive and false-negative rates. We will develop radiomics-based classifiers to predict 5-year DFS.

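### The 5-year imaging and radiomics analyses use DFS, which counts every death, although the stated imaging aim is recurrence and disease control; deaths without recurrence dilute the apparent performance of imaging.

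*Protocol article*

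**What the plan says.** **Outcome definition.** Study Design lists as a secondary endpoint "5-year disease-free survival (DFS) as a composite of BF, patient death, or development of clinical metastases or institution of salvage ADT". The Disease-Free Survival section repeats the composite: "Five-year DFS will be determined as a composite of biochemical control, patient death or development of clinical metastases, or institution of salvage ADT". Neither text limits death by cause, and the plain reading is death from any cause.

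**Where DFS is used for imaging.** Study Design looks for imaging biomarkers "that predict for 5-year DFS". Translational Imaging Endpoints regresses 5-year DFS on PET and mpMRI changes at 6 and 24 months, and adds: "We will develop radiomics-based classifiers to predict 5-year DFS".

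**What the imaging is for.** The Introduction says that the serial imaging should serve "to non-invasively identify early treatment failure". Study Design asks whether a "negative posttreatment PSMA PET/MRI is correlated with a negative 2-year posttreatment biopsy and long-term disease control". The Discussion asks whether patterns of imaging change can be early markers of recurrence. The Abstract and Discussion plan to correlate imaging with PSA and biopsy, "with the goal of early, non-invasive, and accurate identification of treatment failure".

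**Other targets.** The support vector machine, random forest and delta-radiomics models predict response, which that section does not tie to a reference outcome. AUC, error rate, false-positive rate and false-negative rate are the listed performance measures. The operating point is where the two error rates are best balanced.

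**The concern.** Failure, recurrence and disease control are properties of the cancer. DFS is also a property of the man's general health. The two part company when a man dies with no evidence of recurrence: he is a DFS event, but not a treatment failure. A prostate PET or mpMRI metric has no reason to predict that death, so a scan that was right about his cancer is counted as wrong.

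With 50 men, recurrences will be few, so a handful of such deaths can be a sizeable part of the event set. For a marker unrelated to other-cause death, the expected effect is to pull the AUC towards 0.5 and to raise the apparent false-negative rate. The longitudinal imaging is the part of the study that the article presents as unique, so its long-term outcome should match the question.

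**Working it through.** The plan gives no figure for this point. Its only power statement (81%) concerns toxicity and has no bearing here. The check is therefore an illustration of size.

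**Inputs**
- n = 50 (Primary Endpoint and Sample Size).
- 5-year recurrence f, low range: 8% and 15%, the complements of the 92% and 85% 5-year biochemical DFS in Table 1.
- 5-year recurrence f, higher value: the Introduction cites a retrospective SBRT series with up to 38% positive 2-year biopsies, and 5-year biochemical failure of 57% after a positive and 7% after a negative biopsy. This gives 0.38 × 0.57 + 0.62 × 0.07 = 0.26.
- Death without recurrence d: 1% to 3% per year. **This is assumed; the documents give no rate.**

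**Formulas** (constant competing hazards over 5 years)
- Recurrence hazard λr = −ln(1 − f)/5; death hazard λd = −ln(1 − d).
- Share of DFS events that are deaths without recurrence: s = λd/(λr + λd).
- Expected DFS events: 50 × [1 − (1 − f)(1 − d)^5], split 1 − s to s.
- AUC of a perfect recurrence marker scored against DFS, with men who die without recurrence scoring like event-free men: (1 − s) × 1 + s × 0.5 = 1 − s/2.
- False-negative rate of that marker when the two error rates are set equal: at false-positive rate x, a fraction x of these deaths is also called positive, so the false-negative rate is s(1 − x). Setting s(1 − x) = x gives x = s/(1 + s).

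**Worked case**, f = 15%, d = 1%: λr = 0.0325, λd = 0.01005, s = 0.01005/0.04255 = 0.236. DFS events = 50 × (1 − 0.85 × 0.951) = 9.6, of which 7.3 are recurrences and 2.3 deaths. AUC = 1 − 0.118 = 0.88. Balanced false-negative rate = 0.236/1.236 = 19%.

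| f | d per year | Recurrences | Deaths without recurrence | Share s | AUC, perfect marker | Balanced false-negative rate |
|---|---|---|---|---|---|---|
| 8% | 1% | 3.9 | 2.4 | 38% | 0.81 | 27% |
| 8% | 3% | 3.7 | 6.8 | 65% | 0.68 | 39% |
| 15% | 1% | 7.3 | 2.3 | 24% | 0.88 | 19% |
| 15% | 3% | 7.0 | 6.5 | 48% | 0.76 | 33% |
| 26% | 1% | 12.7 | 2.1 | 14% | 0.93 | 13% |
| 26% | 3% | 12.1 | 6.1 | 34% | 0.83 | 25% |

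A marker with a true AUC of 0.85 would show 0.85(1 − s) + 0.5s: about 0.62 to 0.77 at 8% to 15% recurrence, and about 0.73 to 0.80 at 26%.

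**Lower mortality, simpler count.** Take failures as 50f and deaths among the rest as 50(1 − f)D, with D = 2% to 10% over the whole 5 years (also assumed). The share runs from 0.75/(12.5 + 0.75) = 6% at f = 25% and D = 2%, to 4.6/(4 + 4.6) = 53% at f = 8% and D = 10%.

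If the outcome is recurrence, with other-cause death as a competing event, this loss is zero for a perfect marker in every row.

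**The case against.** **The imaging aims have other comparators.** A reader might infer that the plan defines one failure in two conflicting ways and that the whole imaging programme is compromised. The documents do not support that. The treatment-failure sentence in the Abstract and Discussion names PSA and biopsy as comparators, and neither contains death. The 24-month biopsy is the reference for validating imaging within the prostate. Those analyses stand as planned. The mismatch remains for the 5-year outcome, because disease control and recurrence are stated aims and DFS is the only long-term outcome named for the imaging models.

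**Not every classifier is aimed at DFS.** A reader might also infer that all the listed performance measures are scored against DFS. They follow the models that predict response, and they come before the separate sentence on DFS classifiers. Applying them to the DFS classifiers is a natural reading, but it is not stated.

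**The size rests on inputs from elsewhere.** The 8% to 15% comes from one 35-fraction trial. Its measure is labelled biochemical DFS and may already include deaths, while this trial also enrols very-high-risk and node-positive men. The 26% is an upper-end figure from a series not described as boosted. Mortality is assumed. It would also be wrong to read the death share itself as the false-negative rate: that holds for a binary marker, not at a point that equalises the two error rates. This objection stands, and it is why ranges are shown.

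**DFS with death is conventional, and detail can be left to the analysis plan.** The first part is right for the Kaplan-Meier estimate, which is not criticised here. The second does not dispose of the point, because the article itself states the outcome and its components; an analysis plan that followed it would carry the mismatch forward.

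**Consequences are limited.** No decision rule rests on these models in a 50-man toxicity pilot. A reader might infer that the trial would wrongly conclude that imaging fails to identify failure; the unaffected PSA and biopsy correlations make that too strong.

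Two smaller limits apply. Deaths before the 24-month scan drop out of the 24-month analyses. A death without recurrence in a scan-positive man would be credited as a hit, so individual errors can run either way.

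**Conclusion.** The point holds for the 5-year imaging regressions and the DFS radiomics classifiers. Their outcome counts deaths that the stated aim does not concern, and the expected effect is to understate how well imaging identifies recurrence. Under the assumed 1% to 3% yearly death without recurrence, about 2 to 7 of 50 men are affected. That is 24% to 65% of DFS events at 8% to 15% recurrence and 14% to 34% at 26%. A perfect marker would show an AUC of 0.68 to 0.88 or 0.83 to 0.93 respectively, with a balanced false-negative rate of about 19% to 39% in the lower recurrence range. The direction follows from the definition for any marker unrelated to other-cause death; the size depends on assumed mortality and could be smaller. DFS as a clinical endpoint and the PSA and biopsy analyses are not in question. This is a cheap improvement.

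**What to change.** Keep DFS with Kaplan-Meier as the clinical secondary endpoint. In Translational Imaging Endpoints, and in the biomarker sentence of Study Design:

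- Make recurrence the main outcome of the 5-year imaging and radiomics analyses: the DFS components other than death, plus death from prostate cancer.
- Treat death from other causes as a competing event, through cumulative incidence or cause-specific hazards.
- In the classifiers, do not label a recurrence-free death as a failure, and state in advance how such men are handled.
- Report the analysis against DFS as supportive.
- If the response that the other models predict is meant to be DFS, apply the same rule there.

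The change needs no extra patients or procedures. Cause of death must be recorded, and the imaging models lose the other-cause deaths as events (about 2 to 7 under the assumptions above). It should be settled before outcome data are seen, because a later choice of target would be open to challenge.

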## Discussion/Conclusion

Advanced prostate imaging with mpMRI and novel PET agents has the potential to improve prostate cancer management across the disease spectrum (23). In the primary management of prostate cancer, improved imaging guidance has allowed for radiotherapy advances for prostate cancer, including prostate SBRT and focal boost (3–6, 11). Ongoing trials are evaluating SBRT with focal boost guided by mpMRI and PSMA-PET (NCT04243941, NCT04402151, and NCT04599699) (21, 59). The ARGOS/CLIMBER trial will explore the safety of SBRT with focal boost guided by mpMRI and ^18^F-PSMA-1007 PET.

In addition, advanced imaging has improved the ability to characterize patterns of disease recurrence and identify men with isolated local recurrence who may be suitable for local salvage or oligometastatic recurrence who may be eligible for metastasis-directed therapy (14, 45, 52, 60). To date, response to prostate SBRT is mostly commonly evaluated using biochemical response with the Phoenix Criteria for BF. The drawbacks of this approach include lack of lesion identification, a high false-positive rate, and delay in identifying treatment failure. An important knowledge gap is the expected evolution of imaging changes post-SBRT and whether patterns in these changes can serve as early biomarkers of disease recurrence. Patients in ARGOS/CLIMBER will receive dynamic ^18^F-PSMA-1007 PET and mpMRI prior to SBRT and at 6 and 24 months after SBRT. Imaging findings will be correlated with PSA and biopsy results, with the goal of early, non-invasive, and accurate identification of treatment failure.

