Another application for advanced imaging in SBRT prostate treatment is in response assessment. To date, evaluation of success following SBRT is most commonly by biochemical means, and successful SBRT is associated with low PSA nadirs comparable to those noted with brachytherapy (34). Biochemical control is a suboptimal method to assess recurrence in patients due to a lack of spatial information, potential false positives, and delayed identification of failure based on rising PSA. First, the lack of lesion identification using PSA-based criteria alone prevents successful local or metastasis-directed salvage without the use of imaging. Given the potential toxicity of local salvage, identification of isolated local recurrence is critical (14). Secondly, the Phoenix Criteria has a false-positive rate in patients who receive SBRT. In a multi-institutional pooled analysis of over 2,000 patients who received prostate SBRT, the Phoenix Criteria was associated with a false-positive rate of 30% (35). Finally, the Phoenix Criteria occurs late. Patients who have local failure may not reach the Phoenix Criteria for years and may lose the opportunity for successful local salvage. A retrospective study showed that up to 38% of patients who received SBRT to doses of 32.5 Gy or higher in 5 fractions had a positive prostate biopsy 2 years after SBRT (36). However, just 12.5% of these patients had reached the Phoenix Criteria at the time of biopsy. Even in patients with a PSA of less than 1 ng/ml prior to biopsy, up to 25% of patients had a positive biopsy (36). Most patients with a positive 2-year biopsy would reach BF at 5 years (57% vs. 7% as compared to those with a negative biopsy), even after 35% of patients with a positive 2-year biopsy received salvage therapies. In another retrospective study, 63 patients, mostly with high-risk prostate cancer (40/63, 64%), received PSMA-targeted PET/CT for rising PSA that did not meet the Phoenix Criteria after primary conventional or moderately hypofractionated EBRT (37). Median rise above nadir PSA prior to PET was 1.2 ng/ml, and median PSA was 1.3 ng/ml. Recurrence was detected in 84% of patients (53/63). While 21/63 patients (33%) had local recurrence only, 14/63 (22%) had nodal recurrence without distant metastases, and 18/63 (18%) had distant metastases. Given the efficacy and toxicity of curative-intent local salvage treatments, improved and early identification of isolated local recurrence is needed (14, 15).

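### The analyses of imaging against 5-year DFS name no PSA covariate or PSA-only benchmark, so a scan that largely mirrors PSA could appear to be a new early marker

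*Protocol article*

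**What the plan says.** The Introduction and Background makes the case for imaging against PSA: "Biochemical control is a suboptimal method to assess recurrence in patients due to a lack of spatial information, potential false positives", and late recognition of failure is listed as a third drawback. The Abstract and the Discussion/Conclusion repeat the argument, and the latter states the aim: "Imaging findings will be correlated with PSA and biopsy results, with the goal of early, non-invasive, and accurate identification of treatment failure".

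The outcome analyses are under Translational Imaging Endpoints:

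- "We will correlate changes in PET and mpMRI metrics at 6 and 24 months with 5-year DFS using linear regression models".
- Support vector machine and random forest classifiers predict response from pretreatment images, and a delta-radiomics analysis uses the first two time points. Also: "We will develop radiomics-based classifiers to predict 5-year DFS".
- "We will measure the performance of the classifiers using a cross-validation design, with metrics including the area under the receiver operating characteristic (ROC) curve", together with error, false-positive and false-negative rates.

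DFS is defined under Disease-Free Survival: "Five-year DFS will be determined as a composite of biochemical control, patient death or development of clinical metastases, or institution of salvage ADT".

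On timing, Study Design says "Serial PSMA PET/MR images will be collected at baseline, 6 months, and 2 years". The Table 4 row "PSA and testosterone" is marked at 6 and 24 months, the same visits (V7 and V10) as the two post-treatment scans. Pretreatment PSA is marked one week before the baseline scan.

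Study Design also plans to relate a negative post-treatment scan to a negative 2-year biopsy, and to correlate 4-year PSA response with imaging and DFS.

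**The concern.** When a new marker is justified by the shortcomings of an existing one, the useful question is comparative: does the scan tell more about later failure than the PSA taken at the same visit? The DFS analyses named in the article do not ask this. They relate imaging to DFS with no PSA model beside it.

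Two features make this matter. Biochemical failure is part of DFS, so PSA is built into the outcome. The protocol also treats PSA as prognostic: it links successful SBRT to low PSA nadirs and lists 4-year PSA response as a candidate prognostic biomarker. A scan metric that tracks PSA would therefore tend to show an association with DFS even if it carried no further information about prognosis. The trial could then not say whether two extra PET/MRI examinations predict failure better than a blood test already taken.

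**Working it through.** **The plan's own figure.** None is given for the imaging analyses. The only design calculation is for toxicity (n = 50, null rate 0.30, assumed rate 0.15, one-sided 0.05):

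Φ{(0.30 − 0.15 − 1.645·√(0.30·0.70/50)) / √(0.15·0.85/50)} = 80.5%, against 81% stated.

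It reproduces but has no bearing here.

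**What each planned comparison can show**

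| Planned comparison | What it shows | Added value over same-visit PSA? |
|---|---|---|
| Imaging change vs 5-year DFS | Marginal association | No, as named |
| Classifiers, cross-validated AUC | Discrimination of imaging alone | No benchmark named |
| Imaging vs PSA | Overlap of the two | No |
| Imaging vs 2-year biopsy | Agreement with a standard not built on PSA | No PSA comparator named |
| 4-year PSA response vs imaging and DFS | Relation to a later PSA measure | No; it follows both post-treatment scans |

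**Size, survival version (every input assumed except n = 50).** Let z be standardised log PSA, let the scan be x = ρz + independent noise, and let the hazard depend on z only. Take ρ = 0.4–0.8 and a hazard ratio of 2.0–2.7 per SD of z. Five-year DFS of 75% gives 50 × 0.25 = 12.5, about 12 events; 85% gives 50 × 0.15 = 7.5, about 8 events.

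- Scan alone nominally significant: 15–69% of trials at 75% DFS and 10–50% at 85%.
- Likelihood-ratio test for the scan given PSA: positive in 4–7%.
- A repeat with 800 trials per setting gave 14–68%, 9–51% and 3–8%. Linear regression of DFS status, the model type the article names, gave 14–68% and 10–52% for the scan alone.

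**Size, linear-regression version (wider assumed grid, 4,000 trials per setting, two-sided 0.05).** PSA is normal with a shift d = √2·Φ⁻¹(AUC) in men who fail. The scan is x = ρ·PSA/s + √(1 − ρ²)·noise, where s is the SD of PSA. The entries are the percentage of trials in which the scan alone is significant:

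| 5-year failure | AUC of PSA | ρ = 0.5 | ρ = 0.7 | ρ = 0.9 |
|---|---|---|---|---|
| 15% | 0.70 | 14.5 | 23.7 | 37.0 |
| 15% | 0.80 | 28.2 | 49.3 | 70.7 |
| 25% | 0.70 | 18.9 | 31.0 | 49.9 |
| 25% | 0.80 | 36.2 | 64.6 | 87.4 |
| 35% | 0.70 | 21.6 | 38.4 | 58.1 |
| 35% | 0.80 | 40.9 | 70.8 | 91.5 |

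With PSA added to the model, every cell falls to between 4.3% and 5.5%.

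**Hand check of one cell (25%, 0.70, ρ = 0.7).**

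- d = 1.414 × 0.524 = 0.742, and s² = 1 + 0.25·0.75·0.742² = 1.103, so s = 1.050.
- Mean difference in scan: 0.7 × 0.742/1.050 = 0.494.
- Within-group SD: √(0.49/1.103 + 0.51) = 0.977. Standardised difference: 0.506.
- Expected statistic: 0.506 × √(12.5 × 37.5/50) = 1.55.
- Φ(1.55 − 2.01) is about 32%, against 31% simulated.

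Both versions count all failures over five years. A landmark would remove early failures, leaving fewer events and lower scan-alone rates.

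**The case against.** The strongest reply has five parts.

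1. *Imaging is not judged on DFS only.* Correct. A reader might infer from the DFS models that no other standard is used, but the article plans biopsy comparison and correlation with PSA. Nor is PSA missing at the scan visits: Table 4 schedules it at both. The gap is that collected PSA is not named in the DFS models.
2. *Correlating imaging with PSA is useful.* Correct. A reader might argue that it works against the aim, since high correlation means imaging adds little. That does not follow. The correlation is the planned step that would reveal mirroring, and a scan correlated with PSA can still locate disease, which PSA cannot. Location is the first drawback of PSA the article lists. But the DFS regressions and classifiers assess prognosis, not location, and there PSA is the natural comparator.
3. *This is a 50-man pilot with a toxicity endpoint, and no rule is given for declaring a marker.* Also correct, so the documents do not support saying the trial will declare false markers. Establishing association before added value is a defensible order. It does not prevent showing PSA performance alongside.
4. *Covariates may be set out in the full protocol or a SAP not shown, and the regressions are not said to be single-predictor.* This cannot be excluded. Still, the article sets out models, outcomes, classifiers and performance metrics, and none of the comparisons it names answers its motivating question.
5. *The simulated excess follows by construction, and an added-value test would be weak.* Both stand. With a scan that truly adds information (assumed independent hazard ratio 1.5–2.0 per SD, PSA hazard ratio 2.0, correlation 0.4–0.8), the power of the added-value test was about 12–54% at 75% DFS and 11–39% at 85%. Requiring a significant result before reporting would usually discard useful markers. This shapes the fix but does not remove the point.

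**Conclusion.** The concern holds in a limited form. The imaging–DFS regressions and the classifiers, as the article describes them, name neither a PSA covariate nor a PSA-only benchmark. Yet the imaging is motivated by the limits of PSA, PSA is drawn at both post-treatment scan visits, and biochemical failure is part of the outcome. A scan that largely repeats PSA could appear to be a new early marker, and correlation with PSA would show the overlap without settling whether imaging adds anything.

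The size is illustrative. For a scan with no information beyond PSA, the scan alone is nominally significant in roughly 10–70% of simulated trials in the survival setting, and in up to about 92% at the extreme of the wider grid. With PSA in the model the rate is about 5%. Only the sample size of 50 comes from the protocol; the correlation, the strength of PSA and the DFS rate are assumptions. The figures show what the named analyses cannot distinguish. They do not predict this trial's result. The point does not touch the toxicity endpoint, and it is an inexpensive improvement to an exploratory analysis.

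**What to change.** - **DFS models.** At 6 and 24 months, restrict to men still event-free at that scan (a landmark analysis) and count DFS from there. Fit DFS on same-visit log PSA alone, then on log PSA plus the imaging metric, using a penalised time-to-event model. Report the change in C-index with its confidence interval. Without the landmark, men who had already failed biochemically by 24 months would be predicted by the PSA that defined their failure.
- **Classifiers.** Report the cross-validated AUC of PSA alone beside each imaging classifier: baseline PSA for those built on pretreatment images, and PSA through 6 months for the delta-radiomics analysis.
- **Reporting.** Label these results exploratory. Do not describe a marker as improving on PSA from an imaging-only association. Do not make a significant added-value test a condition for reporting a marker.

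The cost is a few extra model fits on data already scheduled. Added-value estimates will be imprecise: about 8–12 DFS events in total under the assumed rates, and fewer after the 24-month landmark. The confidence intervals should be shown so that this is visible.
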